# Anaesthetic efficacy and influence on cardiovascular parameters change of intraosseous computerised anaesthesia versus inferior alveolar nerve block anaesthesia in acute irreversible pulpitis of mandibular molars: study protocol for a prospective randomised controlled trial

**DOI:** 10.1186/s13063-022-06915-4

**Published:** 2022-12-05

**Keywords:** Local anaesthesia, Dental anaesthesia, Analgesia, Irreversible pulpitis, Mandibular molars, Dental emergency, Pain management, Pulpotomy

## Abstract

**Background:**

Irreversible pulpitis is a highly painful inflammatory condition of the dental pulp. The recommended care is the removal of the coronal pulp (pulpotomy) for emergency treatment in multi-rooted teeth. However, achieving adequate analgesia in the case of mandibular molars presents many difficulties according to the dental literature. Intraosseous computerised anaesthesia (ICA), in particular, the QuickSleeper™ system, has already been demonstrated to be clinically efficient, but ICA is known to increase the heart rate reversibly in a manner that depends on the speed of injection. Therefore, accelerated heart rate was examined as a potential adverse effect of this injection. This trial aims to compare the cardiovascular effects and the anaesthetic efficacy of ICA versus inferior alveolar nerve block anaesthesia (IANB) in acute irreversible pulpitis of mandibular molars.

**Methods:**

This study is a non-inferiority prospective, randomised, controlled, single-blind, two-group trial conducted at the Nantes University Hospital. The study design included two parallel arms at a ratio of 1:1 that will allocate seventy-two patients into two groups: the first group will receive QuickSleeper™ intraosseous anaesthesia; the second will receive an inferior alveolar nerve block before emergency treatment (pulpotomy). This study will include patients requiring emergency dental care under local anaesthesia with confirmed irreversible pulpitis in mandibular molars. The primary outcome is the time taken for the fluctuations in the cardiovascular parameters to return to baseline values during endodontic treatment in two different anaesthetic techniques. The secondary outcomes include efficacy of the technique, patient’s pain perception before and after care, any post-operative effects, and factors associated with the delay of recovery of cardiovascular parameters between the 2 anaesthetic techniques.

**Discussion:**

This trial will evaluate the factors associated with heart rate increase during local anaesthesia administration. The use of blood pressure and cardiovascular measurements can be considered an asset and additional safety in managing local anaesthesia. Detecting early signs of potential adverse events (AEs), particularly patients with certain medical conditions (cardiac rhythm disorders), would suggest caution in administering anaesthesia.

**Trial registration:**

ClinicalTrials.gov ID: NCT03802305 registered January 14, 2019. (version no. 1.2; 5 November 2021)

**Supplementary Information:**

The online version contains supplementary material available at 10.1186/s13063-022-06915-4.

## Background

Irreversible pulpitis is based on subjective and objective findings that the inflamed vital pulp is unable to heal, as a result of bacterial infiltration [1]. The common symptoms include intense and paroxysmal spontaneous pain exacerbated by certain stimuli such as sweet, hot or cold foods and beverages [2]. However, relying on symptoms alone is not always clinically indicative of irreversible pulpitis because the tooth may occasionally appear asymptomatic and responds well to thermal testing. In such cases, dental history and thermal testing are the primary tools for assessing pulpal status. Furthermore, irreversible pulpitis is one of the most common reasons for emergency consultations in dentistry [2].

The treatment of choice is a pulpectomy, i.e. complete removal of pulp tissue. In an emergency appointment, however, due to time constraints, this treatment could be challenging to perform. In multirooted teeth, it is commonly accepted that a pulpotomy, within part of the pulp tissue, removed at the level of the dental crown, is performed. The purpose of an emergency pulpotomy is to stop the pain of pulpitis and results in a lower incidence of postoperative pain [3–6]. The standard anaesthetic technique is an inferior alveolar nerve block (IANB) by introducing the needle near the mandibular foramen at the spine of Spix.

Obtaining anaesthesia in patients with endodontic pain of pulpal origin is often difficult to achieve despite supplemental buccal infiltrations in addition to nerve blocks [7]. The failure rate is between 44 and 81% as was described in various clinical studies [8–10]. In addition, mandibular molars are the most difficult to anaesthetise [11]. In mandibular molars, there is an IANB failure rate of 15% up to 58% for non-inflammatory pulpitis [12, 13] and 44 to 81% for irreversible pulpitis [14–17]. IANB is performed blindly and guided only by anatomic landmarks that vary from individual to individual. Furthermore, there is a variation in the physicochemical characteristics such as lowered pH in the inflamed tissue that neutralises the base form of the anaesthetic in the nerve sheath and membrane. Furthermore, there are altered resting potentials and lowered thresholds of the excitability of the nerves in the inflamed tissue that leads to a varied state of innervation [18]. In addition, psychological factors (fear, anxiety) from one individual to another leads to a state of hyperalgesia or no analgesia that adds to the difficulties in achieving successful pulpal anaesthesia.

Anaesthetics called intra-osseous (IO) could be a more effective alternative. IO consists of depositing the anaesthetic solution into the alveolar bone supporting the teeth. In this method, anaesthesia begins immediately after the injection without causing soft tissue numbness. The injection scarcely causes any pain, and it requires relatively fewer amounts of the anaesthetic solution compared to conventional nerve block techniques [19, 20]. Several types of intraosseous anaesthetic system have been commercialised and studied clinically, such as the Wand® (Milestone Scientific, USA), the X-Tip (Dentsply, York, PA) and Stabident™ (Fairfax Dental Inc., Miami, FL) systems.

Several forms exist: intra-septal (IS), intra-diploid (ID), and more recently, intra-osseous computerised anaesthesia (ICA). However, IS administers the anaesthetic solution into the bone septum just after the cortex, a dense and reduced area, that may lead to partial or complete necrosis [21].

Intra-osseous computerised anaesthesia (ICA), such as the QuickSleeper™ system (Dental Hi-Tec, Cholet, France), administers the solution with a computerised control into the diploë (a richly vascularized bone) at a local rate and pressure. Thus, the QuickSleeper™ system is a form of ID in which the anaesthetic is delivered close to the root apices and associated periradicular tissues, leading to a greater reduction in periradicular sensation. The anaesthesia takes effect more rapidly since the solution is deposited close to the apex of the tooth at an axis of 15° to 30°. Thus, this form of delivery increases its effectiveness and reduces the risk of tissue necrosis, with better pain control (42 to 93% according to studies) [22, 23]. No soft tissue numbness occurs, and relatively fewer amounts of anaesthetic solution are needed. However, due to the fast diffusion of the anaesthetic solution in the diploe, the heart rate accelerates via the added effect of vasoconstrictors. This elevation is transient, and its effect is negligible and does not pose serious cardiovascular risk [12, 22].

There are currently many clinical studies that have evaluated cardiac parameters during IO administration. The heart rate increases in a reversible manner depending on the speed of injection [12]. The Stabident™ system showed a significant increase in heart rate of 8-28 beats/minute (BPM) on average with 2% lidocaine 1:100,000 epinephrine according to 3 authors [24–26]. By comparison, the X-Tip injection elevated the heart rate by 9–10 beats per min [27]. In regard to other parameters such as oxygen saturation and blood pressure, Pereira et al found no differences in either of them when using the X-Tip™ system but noted a significant increase in heart rate with 4% articaine (1:100,000 or 1:200,000 epinephrine) for anaesthetizing irreversible pulpitis lower molars [23]. Therefore, the accelerated heart rate could be a potential adverse effect of this injection [27].

Articaine is a common anaesthetic agent and a member of the amide family. The presence of its thiophene group increases its liposolubility, facilitating its diffusion into both nerve sheaths (such as the inferior alveolar nerve) and neural membranes of individual axons comprising a nerve trunk. The lower pKa of articaine would translate into a greater percentage of the drug in the active base form and its plasma protein binding is 95% higher than most other local anaesthetics [25–27].

The use of epinephrine allows an increase in the success of anaesthesia and a decrease in systemic toxicity, with better pain control. Rogers et al. published the first randomised, double-blind, clinical trial of the efficacy of 4% articaine versus 2% lidocaine in an IANB. They found that 4% articaine was significantly more effective than 2% lidocaine, with success rates of 62% and 37%, respectively [28].

There are even fewer studies on the QuickSleeper™ system and the variations in cardiovascular parameters (heart rate, systolic and diastolic blood pressure) that occur before and after anaesthesia administration. One study concluded that the increase in heart rate parameters caused by IO injection compared with IANB conventional block in impacted mandibular third molars was not significantly different [29]. However, there was no controlled concentration of epinephrine and no proper monitoring of the effects of anaesthesia.

### Objectives

The protocol mainly aims to compare the cardiovascular effects and the anaesthetic efficacy of intra-osseous computerised anaesthesia (ICA) versus inferior alveolar nerve block anaesthesia (IANB) in acute irreversible pulpitis of mandibular molars. The primary objective will be the evaluation of the time taken for the cardiovascular parameters to return to their initial values before administration of ICA compared to IANB in a mandibular molar presented with irreversible pulpitis. Secondary objectives will be the efficacy of the QuickSleeper™ system compared to IANB when (i) comparing patient pain, (ii) comparing postoperative outcomes, and (iii) investigating factors associated with the time to recovery of cardiovascular parameters between the 2 anaesthetic techniques. The use of blood pressure and cardiovascular measurements can be considered an asset and additional safety in the management of local anaesthesia through the early detection of signs of potential AEs. The main risk associated with local anaesthetics is a hypersensitivity or toxicity reaction, which is considered to be low leading to a very favourable benefit/risk balance.

## Methods/design

The trial protocol is identified as version n°2.0 of 11 December 2019. It adheres to Standard Protocol Items: Recommendations for Interventional Trials (SPIRIT) criteria; the SPIRIT Checklist can be found as Additional File 1: Table S1.

### Design

This noninferiority, prospective, randomised, controlled, single-blind, two-group study will be conducted in the emergency subunits of the Nantes University Hospital. Eligible patients with irreversible pulpitis in the first or second mandibular molars requiring emergency dental care will be included in the study. Diagnosis will be based on clinical and radiographic examination. Two parallel groups will be randomised at a ratio of 1:1 so that patients will either receive (1) intraosseous anaesthesia or (2) inferior alveolar nerve block anaesthesia. This manuscript used the SPIRIT reporting guidelines [30].

### Involvement in the design of the protocol

No members of the public or patient groups were involved in the design of the protocol.

### Participants

Adult patients seeking emergency consultation at the dental department of Nantes University Hospital will be included in the study according to the following criteria:Presence of spontaneous and/or diffuse pain with severe sensitivity to cold and/or heat tests in the first or second mandibular molarPatients over 18 years old (of any gender)Patients in good health, with no medical history (ASA 1 score) and no drug treatment for cardiac rhythm disorders (antiarrhythmics, beta-blockers)Patients able to give his/her oral consent.Affiliated with a health insuranceAgree to be contacted by phone 72h after the emergency treatment

Participants will not be included if they present at least one of the following non-inclusion criteria:Contraindications to anaesthesia with vasoconstrictorsDiagnosis of irreversible pulpitis of third mandibular molars, reversible pulpitis, acute apical periodontitis, periodontal lesion of endodontic origin or dentin syndromeNon retainable tooth requiring extractionVital tooth serving as an abutment in fixed prosthesisPatients under the age of 18Adult patients who do not understand French or have refused to consent will not be able to participatePregnant or breastfeeding women

### Outcomes

The main outcome of this study is to compare the time required in minutes for the cardiovascular parameters to return to their initial values between the two techniques: ICA with the QuickSleeper™ system versus the reference technique: inferior alveolar nerve block (IANB). The timing of the evolution of the parameters is based on 3 phases: “baseline” from T0 to T+4 minutes, “anaesthesia” from T+4 to T+8 minutes, and “pulpotomy” from T+8 to T+14 minutes. The return to baseline values will be defined as a success if 3 successive values of heart rate and blood pressure (systolic and diastolic) are identical to those recorded before injection. On the other hand, if there is an absence of 3 successive values of these two parameters, it is defined as a failure.

Secondary outcomes include:The O^2^ measurement performed during the 3 phasesThe efficacy of the anaesthesia with a VAS (visual analogue scale) of 0 and that the pulpotomy was completed successfully: the patient is asked about his or her perception of pain before the operation at D0 and D+1, D+2, and D+3Post-operative careInvestigation of factors associated with delay in recovery of cardiovascular parameters (heart rate, dental anxiety, age, gender, and use of analgesics in the 6 h before surgery)

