### Sequence generation

Each patient, regardless of the study group allocated, will receive 1.8 mL of 4% articaine 1:100 000 for 2 min. The evaluated intervention consists of the administration of intraosseous anaesthesia using the QuickSleeper™ (DHT, Cholet, France) system, according to the manufacturer’s recommendations, in the “ICA” group. A plastic syringe with a cartridge of 4% articaine 1:100,000 epinephrine will be used in the “IANB” group. The emergency treatment will be a pulpotomy. The tooth will be isolated with a rubber dam and all carious tissue and pulpal parenchyma will be removed. Pulpal bleeding will be controlled using a 2.5% sodium hypochlorite and the site will be covered with calcium hydroxide and a temporary filling. At the end of the intervention, all patients, regardless of the randomisation group, will be given two types of antalgics (paracetamol 1 g or paracetamol 600mg/codeine 50 mg) according to preoperative pain declaration (VAS) and recommended to take them only if they experience pain, according to the good clinical recommendations.

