### Statistical analysis

The analysis will be based on intention-to-treat (ITT) using the “missing=failure” strategy. A robustness analysis, supported by the per-protocol approach, will be carried out if the patients present with protocol deviations (error of randomisation). Qualitative variables will be described by the percentages and numbers of each modality. Quantitative variables will be described by means and standard deviations. Confidence intervals at 95% will be presented.

A paper case report form (CRF) will be created for each patient inclusion for data collection and will be based on the establishment of a clinical database. All information required by the protocol must be provided in the CRF, necessary for statistical analyses.

To assess the primary endpoint (time to return to baseline heart rate and blood pressure), the mean values will be estimated by the Kaplan-Meier method (survival curves) and compared using Log-Rank tests. To assess the secondary endpoint (time to baseline O_2_ and change in measurements over time), the 2 arms will be compared in the same way as the heart rate and blood pressure parameters. Univariate and multivariate Cox models will be used to investigate the factors associated with the time to the baseline of cardiopulmonary constants. The difference in pain between D0 and D+3 will be compared between the 2 groups a Student’s *t*-test or a Wilcoxon test. Data for the analysis are collected from the first questionnaire (French version of Corah’s dental anxiety scale), the three phases of cardiopulmonary monitoring, the VAS assessment, and the postoperative questionnaire given to the patient at the end of the procedure. The information recorded on the postoperative questionnaire will be collected by a telephone call 3 days after the procedure. All the data collected will be typed and inserted into an Excel spreadsheet for data entry in a secure computer network of Nantes University Hospital. The investigative team, mainly the investigators as well as the study technicians involved in this study protocol will have access to the data collected.

In regard to the post-trial care, the patients will either continue their dental care with their appointed dentist, or in the case where they do not have one, they will be following appointments at the Nantes University Hospital.

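### The primary endpoint scores a return to baseline without requiring a prior departure, so pre-rise readings can end the clock and patients who never rise have no defined place

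*Protocol article*

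**What the plan says.** The Outcomes section of the protocol article sets the main outcome as "the time required in minutes for the cardiovascular parameters to return to their initial values between the two techniques". It then gives both halves of the scoring rule. Success is "defined as a success if 3 successive values of heart rate and blood pressure (systolic and diastolic) are identical to those recorded before injection". Failure is the complement: "if there is an absence of 3 successive values of these two parameters, it is defined as a failure".

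The abstract (Methods) describes the same outcome as recovery from a disturbance: "The primary outcome is the time taken for the fluctuations in the cardiovascular parameters to return to baseline values during endodontic treatment".

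On timing, Outcomes places the anaesthesia phase "from T+4 to T+8 minutes" and the pulpotomy phase from T+8 to T+14. Under Sequence generation each patient "will receive 1.8 mL of 4% articaine 1:100 000 for 2 min". The Statistical analysis section takes the resulting time to Kaplan-Meier curves and log-rank tests, adds no further condition on the event, and treats "time to baseline O_2_ and change in measurements over time" in the same way as a secondary endpoint.

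**The concern.** A return presupposes that something left. The rule checks only that three successive readings match the pre-injection values, so two kinds of patient can be scored without any recovery having been observed.

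- **Pre-rise matches.** A patient whose heart rate will rise gives three readings at baseline before the rise begins. The event is scored and the later rise no longer counts.
- **Patients who never depart.** Under a workable tolerance they score as recovered at the earliest readings. Under exact identity, ordinary reading noise makes most of them failures. Neither result describes recovery, and the rule offers no third category.

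The Discussion states that the aim is to conclude that return times are similar in the two techniques, and intends the result to inform risk with the intraosseous technique. An endpoint that mixes recovery times, pre-rise readings and undisturbed patients can show similarity, or a difference, for reasons unrelated to recovery.

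**Working it through.** No figure in the article bears on this point, so there is none to reproduce. The check has two parts: what the rule implies as worded, and how often it would matter under stated assumptions.

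**1. From the wording.** Abstract: fluctuations return. Outcomes, success: three successive matching readings. Outcomes, failure: no such run. Statistical analysis: time to that event. None of these requires a departure, an earliest start for the run, or a treatment of patients without a departure. The gap follows from the text alone.

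**2. When a pre-rise match is possible.** Take readings every *d* minutes, the first one interval after T+4, with the injection assumed to start at T+4. The third reading falls at 3*d*. A pre-rise match needs 3*d* ≤ onset of the rise.

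- 30-second readings: 3 × 0.5 = 1.5 min, so possible for onset at 2 or 3 min, not at 1 min.
- 1-minute readings: 3 × 1 = 3 min, so possible only for onset at 3 min.
- 2-minute readings: 3 × 2 = 6 min, so not possible for onset up to 3 min.

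If a reading at T+4 itself counts, which the text does not exclude, the condition becomes 2*d* ≤ onset, and 30-second readings allow a match even at 1 min.

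**3. How often, under assumed inputs.**

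- From the article: a window of 14 − 4 = 10 min after the baseline phase, and a 15 bpm rise, chosen inside the 8–28 bpm that Background reports for another intraosseous system.
- Assumed: reading noise SD 3 bpm with lag-one correlation 0.3; a linear rise over 1 min, then exponential decay with a 2-min constant; heart rate only.

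The event is the first reading at which it and the two before it all lie within the tolerance. It is pre-rise if that reading is no later than onset. Exact identity is taken as the same whole bpm (±0.5).

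| Tolerance | 30-s readings, onset 2 min | 30-s, onset 3 min | 1-min, onset 3 min | Never-rise patient scored at first three readings |
|---|---|---|---|---|
| Identity | 0.5% | about 1% | 0.2–0.3% | 0.2–0.3% |
| ±3 bpm | 43% | 64% | 33% | 33% |
| ±5 bpm | 81–82% | 95% | 75% | 75% |
| ±8 bpm | 99% | over 99% | 98% | 98% |

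Every other combination of these intervals with onset at 1, 2 or 3 min gives 0%. If a T+4 reading counts, the ±5 bpm shares for onset at 1, 2 and 3 min become 75%, 89% and 97% with 30-second readings, and 0%, 75% and 82% with 1-minute readings.

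Hand check of the last column, ignoring correlation: at ±5 bpm one reading is in tolerance with probability 1 − 0.096 = 0.904, and 0.904³ = 0.74. At identity the probability is 0.132, and 0.132³ = 0.0023. Under identity a never-rise patient meets the rule anywhere in the window in only about 4% (30-s readings) or 2% (1-min) of cases, so most are scored as failures.

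**4. Effect on the measured time.** A separate noise-free calculation assumed elevations averaging 3 min (exponential), onset at 1 or 2 min and readings every 0.25 to 2 min. Where three readings fit before onset, the median scored time is 0.75 to 1.5 min, against 3.75 to 5.5 min among patients who rise when a prior departure is required. Over all settings, the share of scored events with no prior rise is 21% to 100% if 80% of patients rise, and 72% to 100% if 30% do.

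**The case against.** The strongest reply is that the high percentages do not describe the rule as written. The article requires identity, and under identity pre-rise scoring is about 1% or less. They also need short reading intervals and a late onset, neither of which is documented. Background describes fast diffusion in the diploë, which points to an early onset, and the article does not say that the injection starts exactly at T+4. All of this stands, and it is why only a range can be given. It does not rescue the rule: identity is itself unworkable with noisy readings, and once a tolerance replaces it this gap becomes material.

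It can also be said that the intent is clear from the abstract, and that reading interval and clock origin may sit in the full protocol. That is fair for those details. But the article states success and failure completely, and as stated they omit the departure that the abstract presupposes.

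Three stronger readings are tempting and are not supported.

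- *That the article expects blood pressure not to rise.* Background cites one study of another intraosseous system that "found no differences in either of them" (oxygen saturation and blood pressure). A group-level result with another device makes non-risers plausible, not established. The argument also needs per-parameter scoring. Outcomes reads as a joint event, in which a heart-rate rise would block the event even if pressure stayed flat; the three criteria at 1.7% under Determination of sample size suggest separate events.
- *That the flaw favours a finding of similarity.* Pre-rise matches pull the arms together, but more non-risers under IANB would make ICA look slower.
- *That the oxygen endpoint should be replaced.* It shares the gap, but the plan already looks at its change over time, and another summary would be a matter of preference.

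**Conclusion.** The point holds as a defect in the definition of the primary event. The rule can count an undisturbed patient, or a patient not yet disturbed, as recovered, and so does not measure the construct that the abstract names. This rests on the wording alone.

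Its size is not determined by the article. Under the assumptions shown, pre-rise scoring ranges from 0% to 95% or more, depending on reading interval, onset and tolerance, and is about 1% or less under exact identity. The treatment of never-rise patients switches from mostly failures under identity to mostly early recoveries at ±5 bpm or wider. No direction of bias can be asserted. The definition should be repaired before the primary comparison is read, because either direction leaves that comparison hard to interpret.

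**What to change.** Make these changes together with replacing identity by a stated tolerance:

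1. State whether the event is joint or per parameter, reconciling Outcomes with the three criteria under Determination of sample size.
2. State the clock origin.
3. Score a return only as the first of three successive in-tolerance readings after the last post-injection departure beyond tolerance.
4. Set the time to 0 by rule for patients with no departure.
5. Report the proportion with a departure, by arm, beside the time comparison.

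Set the tolerance against reading noise. Under the same assumptions, at ±5 bpm with 30-second readings, about 85% of never-rise patients would show at least one stray reading outside tolerance, against 14% at ±8 bpm. Requiring two successive readings for a departure lowers the ±5 bpm figure to about 21%.

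The cost is a rescoring of readings already recorded, with no extra patients or procedures. Some patients will have a time of 0 by rule. Trial status says inclusion was due to end on 1 July 2022, so the definition should be written down and dated before any unblinded analysis.

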### Determination of sample size

The sample size calculation was based on the noninferiority hypothesis in a pilot study that there will be an expected mean difference of 1 min 30 s between the two anaesthetic techniques with regard to the time taken for the values to return to the initial ones. According to the reported results from the few studies available, the proportion of patients having successful anaesthesia and better pain control in the reference group (intraosseous anaesthesia) would be 93%. The noninferiority margin was defined as 20%. The significance was set at 1.7% for the 3 main criteria (heart rate, systolic and diastolic blood pressure) and 5% for the secondary criteria. Thus, using a bilateral test with an epiR package 0.98-87 (Biostatgv), 72 patients (36 patients per arm) will be included in the study.

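### The return-to-baseline event is defined jointly for heart rate and both pressures, but the error rate is split over three separate criteria; read literally, the joint event can mask a heart-rate delay

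*Protocol article*

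**What the plan says.** The Outcomes section is the only place that defines the primary event. Return is a "success if 3 successive values of heart rate and blood pressure (systolic and diastolic) are identical to those recorded before injection", and "if there is an absence of 3 successive values of these two parameters, it is defined as a failure". Both sentences treat heart rate and blood pressure as one package.

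Determination of sample size treats them as three: "The significance was set at 1.7% for the 3 main criteria (heart rate, systolic and diastolic blood pressure". The test is two-sided, with 36 patients per arm, and a mean difference of 1 min 30 s in return time is mentioned.

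Statistical analysis does not settle the matter. It opens with "To assess the primary endpoint (time to return to baseline heart rate and blood pressure", which fits a joint time. It then says that "the mean values will be estimated by the Kaplan-Meier method (survival curves) and compared using Log-Rank tests", where the plural fits several tests.

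On the hazard, the abstract says that "accelerated heart rate was examined as a potential adverse effect of this injection". The Background cites a study of another intraosseous device (X-Tip) that found no differences in blood pressure or oxygen saturation but "noted a significant increase in heart rate with 4% articaine (1:100,000 or 1:200,000 epinephrine". The Discussion states the aim of concluding that return times are similar with the two techniques.

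**The concern.** A joint event and three separate criteria are different endpoints. Under the first, each patient has one return time and there is one comparison. Under the second, each patient has three return times and there are three comparisons, each at about one third of 5%. An analyst who takes the event from Outcomes has nothing to spend the second and third 1.7% on. An analyst who takes the three criteria from the sample size section has no event definition for any of them.

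The choice matters because the joint time is at least as long as the slowest of the three series. If pressures return slowly, or their readings fluctuate so that three matching values in a row are rare, the joint time is driven by pressure. A delay confined to heart rate then shows up only in part. In a trial that hopes to find similar times, this loss of contrast works towards the desired conclusion, and it does so for the parameter that the article names as the safety concern.

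**Working it through.** **Step 1: what the 1.7% implies.** 0.05 / 3 = 0.0167, which rounds to 1.7%; 3 × 1.7% = 5.1%. The figure is a Bonferroni split over three tests and has no purpose if there is a single joint test.

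**Step 2: heart rate alone.** From the article: 36 per arm, two-sided 1.7%, difference 1.5 min. Assigning the whole 1.5 min to a heart-rate delay with ICA is an assumption, because the article gives it for return times in general and without direction. SD 2 min is also assumed, because the article gives none.
- Standard error = 2 × √(2/36) = 0.471 min
- 1.5 / 0.471 = 3.18; critical value z(0.9915) = 2.39
- Chance of detection = Φ(3.18 − 2.39) = 0.79

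Conversely, 36 per arm with 80% power would need SD = 1.5 × √18 / (2.39 + 0.84) = 1.97 min, so SD 2 is in line with the stated size. This does not reproduce the article's 72, which rests on a 93% anaesthetic success rate and a 20% margin, with no power stated.

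**Step 3: joint time.** Joint time = the maximum of the heart-rate, systolic and diastolic times. Assumptions: gamma-distributed times; heart-rate mean 3 to 4 min with IANB and 1.5 min longer with ICA; pressure times equal in both arms; correlation 0 to 0.6. Mean differences and SDs were simulated and put into the formula of step 2.

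| Pressure return: mean, SD (min) | Difference in joint time (min) | Chance of detection |
|---|---|---|
| 0.5 to 1, SD equal to mean | 1.3 to 1.5 | 0.70 to 0.79 |
| 1, SD 2 | 1.2 to 1.4 | 0.40 to 0.58 |
| 2, SD 2 | 1.0 to 1.3 | 0.30 to 0.59 |
| 3 to 5, SD 2 | 0.2 to 1.1 | 0.02 to 0.44 |

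Both the length and the spread of pressure recovery matter: at a mean of 1 min, raising the SD from 1 to 2 takes detection from about 0.70 or more to 0.58 or less.

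**Step 4: check with the planned test.** Log-rank at two-sided 1.7%, 36 per arm, a 10 min window (T+4 to T+14), heart-rate means 4.0 and 2.5 min, coefficient of variation 0.5. Heart rate alone: 0.92. Joint time: 0.92 if pressure return takes no time, then 0.91, 0.73, 0.29, 0.09 and 0.02 at pressure means of 1, 2, 3, 4 and 6 min. The level differs from step 3 because the assumed spread is smaller, but the pattern is the same.

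**Step 5: noise without any drug effect on pressure.** Assume one reading a minute, noise SD of 3 bpm, 5 mmHg (systolic) and 3.5 mmHg (diastolic), and a mean heart-rate rise of 20 bpm with ICA against 5 bpm with IANB. Counting readings within 3 units of baseline as returned, detection is 0.92 on heart rate and 0.03 jointly. Within 5 units it is 1.00 and 0.50. Within 5 bpm and 10 mmHg both are 1.00. With exact identity, as Outcomes words it, about 0.5% (ICA) and 1.2% (IANB) of patients succeed even on heart rate, and neither rule detects anything.

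**The case against.** The strongest reply is that the sample size section already gives heart rate its own criterion at 1.7%, and that the plural tests in Statistical analysis agree. On that reading nothing is diluted. This stands as far as intent goes: the documents do not establish that the joint time will be analysed. But no return event is defined for any single parameter, so the intended reading still needs a change in Outcomes.

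Second, a reader might infer from the Background that only heart rate moves. The article does not support this. The pressure finding comes from one study of a different device. The same section says that cardiovascular data on QuickSleeper are scarce, and cites a study in which the heart-rate increase with intraosseous injection did not differ significantly from IANB, although it faults that study's monitoring. The inference would also undercut the concern: if pressures stayed at baseline and were read without noise, the joint time would equal the heart-rate time (0.92 against 0.92 in step 4). Masking needs slow or noisy pressure readings.

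Third, a reader might conclude that heart rate should be the sole primary criterion. The abstract and Objectives speak of cardiovascular parameters in the plural, and demoting blood pressure would narrow the safety question. That is a debatable trade-off and not something the documents call for.

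Fourth, the exact-identity requirement is a problem of its own, as step 5 shows. Separate scoring does not cure it.

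**Conclusion.** The contradiction is established by the text: one joint event in Outcomes against three criteria at 1.7% each in the sample size section. Its consequence is conditional. If the joint event is applied literally, the chance of detecting a 1.5 min heart-rate delay falls from about 0.79 to anywhere between almost no loss (0.70 to 0.79, pressures back within about 1 min with little spread) and near-complete loss (0.02 to 0.44, pressures back in 3 to 5 min). The article gives no recovery times, SDs, reading interval or measurement error, so it cannot be said where in this range the trial lies. What can be said is the direction: under these assumptions of equal pressure recovery in both arms, any loss favours a conclusion of similar times. A claim that the trial is certain to miss a heart-rate delay would go beyond the documents.

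**What to change.** In Outcomes and Statistical analysis, define and score return time separately for heart rate, systolic pressure and diastolic pressure. Test each as one of the three main criteria at 1.7%, as the sample size section already states. Keep the joint time as a descriptive result only.

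State before analysis how the three results combine into the overall conclusion, so that similarity on pressure cannot offset a delay on heart rate.

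The change needs no new data, because all three parameters are monitored throughout the intervention. The cost is a documented amendment of the protocol and analysis plan. Inclusion was due to end on 1 July 2022 and the article appeared on 5 December 2022, so the amendment should be dated and made before the arms are compared; otherwise it would look like a choice of endpoint after the fact.
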